*Study 1a*. This substudy will evaluate the acceptability and functionality of the camera devices in capturing images of food intake, and the accuracy of dietary intake estimation from the images in adults in different laboratory settings, mimicking unique LMIC conditions. These conditions include using foods of Ghanaian and Kenyan origin, eating under low lighting to mimic a scenario of no or inadequate supply of electricity, and communal eating [i.e., where >1 person eats from a shared plate of food (24)]. Dietary intake estimation from the food images will be compared with weighed food records for validation of the passive dietary assessment method in adults as reported elsewhere. Eighteen adults (≥18 y old) of Ghanaian or Kenyan origin living in London, United Kingdom, will be recruited to participate. The inclusion criteria are: an adult of Ghanaian or Kenyan origin; able to eat foods typical of Ghana and Kenya; have no problem with chewing or food allergies; and able to use a wearable camera device during eating. Consenting adults will be brought to the National Institute for Health Research Clinical Research Facility (CRF) at the Hammersmith Campus of Imperial College London for the study visit activities. The participants will be divided into 3 groups of 6 people and will visit the CRF 3 times (once a week). Three devices, the eButton, AIM, and ear-worn device, will be included for testing. On each visit, a standardized weighing scale (Salter Brecknell) will be used to preweigh foods of Ghanaian and Kenyan origin. Preweighed foods will be presented to the participants to eat, and a passive camera device will be used during eating to take time-lapse images or video of their food intake. Participants will be asked to eat until full. Leftover foods will be weighed (postweight) and recorded. The net difference between pre- and postweighed foods will provide an estimate of weighed food record. During the 3 visits, participants will eat under either good lighting, low lighting, or share a plate of food with other participants. At the end of each visit, participants will be given a device assessment form and asked to provide an acceptability rating (ranging from 1 to 5) on comfort and ease of use, willingness to use a similar device in the future, and choice of a device they most prefer among the 3. Study staff at the CRF will take notes of the challenges encountered and/or reported by the participants on the placement of the devices (ergonomics). In addition, an assessor independent to the data collection will conduct an unbiased assessment of the image quality of the devices and completeness of data collection during the eating episodes to determine their functionality. Images of food intake from the devices will be downloaded onto a computer and stored in cloud storage. The stored images will be assessed for dietary intake estimation using image annotation software. Food analysis software (Dietplan7; Forestfield Software Ltd) will be used to estimate energy, macronutrients (protein, carbohydrates, and fat), and a panel of micronutrients in the weighed food portions eaten by the participants.

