#### Study 3: Assessment of the validity of passive assessment method in estimating dietary intake in households in Ghana and Uganda

The purpose of this study is to test the validity of passive dietary assessment method relative to a weighed food record, in estimating an individual's dietary intake. The weighed food record is used as the gold standard method in this study. A tablet-based, interviewer-administered multiple-pass 24-h dietary recall will also be performed for comparison. Portion size picture aids will be used in the 24-h dietary recall.

Local field staff and community leaders will help in identifying 88 households (44 in each country) for enrollment in this study. The criteria for inclusion are the same as those described for Study 2. Foodcam will be mounted in the household's kitchen or cooking area to capture images of food preparation. Household members will be given a camera device to record their whole-day (waking hours) food intake, and the captured images will be used in the estimation of their dietary intake. However, only 2 randomly selected index cases (an adult and a child) in each household will have their corresponding dietary intake assessed using weighed food records and 24-h dietary recall. Dietary intake data from the devices and the 24-h dietary recall will be compared with weighed food records for accuracy evaluation. Prior to using the devices in the households, a questionnaire (similar to that used in Study 2) will be used to understand the structure, composition, and eating habits of the households to help implement a device deployment plan, especially for those who were not recruited in Study 2. To help recognize and effectively manage the data collection and logistical challenges that might arise in this study, this validation study will be conducted in 2 phases:

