The dietary data collected from the households will be taken to the project office, where the images will be downloaded, reviewed, organized by meal, and uploaded onto the study database. Custom software (described below) will be used to identify the foods on the images, and estimate the portion size eaten and its nutritional content. Weighed food record and 24HR data will be analyzed by independent staff using nutritional analysis software (Dietplan) to estimate the nutritional content. The dietary intake from the images and 24HR will be compared with the weighed food record for accuracy evaluation.

The ethics committees (Institutional Review Boards) of University of Georgia, USA, and Noguchi Memorial Institute for Medical Research, Ghana, have approved Studies 2 and 3 for Ghana (approval reference: STUDY00006121 and IRB00001276, respectively). Studies 2 and 3 in Uganda have been approved by Mbale Regional Referral Hospital Research Ethics Committee (MRRH-REC) and the Uganda National Council for Science and Technology (UNCST) (approval reference: MRRH-REC OUT0051/2019 and HS2680, respectively).

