#### Assessment of nutritional content

Nutritional content of foods captured on the images will be assessed using the AIM software as the interface (Figure 3). The AIM software is capable of incorporating different food composition databases, such as the West African Foods database (31), Kenyan Food database (32), UK Integrated Food Composition dataset (33), and the USDA Food Composition databases (34), allowing users to choose from databases. In addition, the AIM software also accepts ad hoc databases, for example, in situations where “back of pack” nutrient data of food brands need to be added. The closest match for foods in this study will be selected, preferentially the West African Foods database for Ghanaian foods and the East African Food database for Ugandan foods. When required these selections will be supported by other food composition databases, such as the USDA and UK databases. The nutrition analysis for each person's daily food intake will be saved and exported to an Excel (Microsoft) file for analysis.

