### Analytical plan

The data analysis plan will be based on comparison of dietary intake estimated using weighed food records, 24-h dietary recall, and the passive dietary assessment method. This will be achieved using the concordance correlation coefficient (CCC) of Lin et al. (37) to assess the extent of agreement in portion size estimation, daily intakes of energy, and macronutrient (carbohydrate, protein, fat, and selected fatty acids) and micronutrient (iron, zinc, vitamins A, B, D, iodine, folate, and calcium) estimates between methods. These comparisons will include the extent of agreement between the passive method compared with weighed food records, and 24-h dietary recall compared with weighed food records. A 95% CI will be calculated for each Lin CCC. The bootstrap method will be used to test whether the Lin CCC between weighed food records and the passive method is different from that between the weighed food records and 24-h dietary recall methods. In addition, Bland–Altman analysis will be used to assess the limits of agreement and examine trends in differences between methods as a function of magnitude of the value, and paired *t* tests will be used to compare the overall bias between method pairs. The passive and 24-h recall methods will be considered accurate when their estimates of nutrient intake are within ±10% of the intake value measured using weighed food records. The analyses will be conducted among the index cases and then stratified by child and adult, rural and periurban/urban, respectively. To explore factors related to the accuracy of the passive and 24-h recall methods compared with weighed food records, absolute or relative deviation, as appropriate, from the weighed food method (gold standard) will be used as an outcome and be analyzed using multiple linear regression (MLR). Candidate predictors in this MLR analysis include demography, education, urban/rural, child or adult.

Currently, we do not have an analysis plan for validation of the data on breastfeeding frequency and duration captured by the eHAT device because there are no comparable analytical methods. However, the use of the device in this study will help us to understand its acceptability and challenges, and help to inform future studies.

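### Study 3 derives passive-method nutrients in AIM but weighed-record and recall nutrients in Dietplan, with no common composition table fixed, so any table or coding difference falls largely on the passive comparison

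*Protocol article*

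**What the plan says.** The Study 3 section of the protocol article gives the weighed record the reference role: "The weighed food record is used as the gold standard method in this study". It then sets out two routes from food to nutrient.

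- **Images.** "Custom software (described below) will be used to identify the foods on the images, and estimate the portion size eaten and its nutritional content". The section on assessment of nutritional content identifies this software: "Nutritional content of foods captured on the images will be assessed using the AIM software as the interface". AIM can hold several databases, including ad hoc ones. The closest match is selected, "preferentially the West African Foods database for Ghanaian foods and the East African Food database for Ugandan foods", with other tables such as the USDA and UK sets in support.
- **Weighed record and 24-h recall.** "Weighed food record and 24HR data will be analyzed by independent staff using nutritional analysis software (Dietplan) to estimate the nutritional content". No composition table is named for Dietplan.

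Study 1a also uses Dietplan for its weighed portions: "Food analysis software (Dietplan7; Forestfield Software Ltd) will be used to estimate energy, macronutrients (protein, carbohydrates, and fat), and a panel of micronutrients".

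The analytical plan compares the passive method and the recall with the weighed record on portion size, energy, macronutrients and micronutrients. It uses Lin's CCC, Bland–Altman analysis and paired t tests. Two conclusions rest on nutrient values. The first is the accuracy rule, under which both methods "will be considered accurate when their estimates of nutrient intake are within ±10% of the intake value measured using weighed food records". The second is the head-to-head test: "The bootstrap method will be used to test whether the Lin CCC between weighed food records and the passive method is different" from the CCC between the weighed record and the recall.

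**The concern.** A nutrient estimate combines two things: which foods were eaten in what amounts, and the nutrient content assigned to each food. Study 3 sets out to test the first. The second can also differ between methods here, because the passive method is converted in one system and the reference in another, and the article does not tie them to the same table, codes or recipes.

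The recall is not exposed in the same way, since it goes through the same software as the reference. The comparison of the two CCCs is therefore not like for like. Separately, a pass or a failure of the passive method under the ±10% rule could come from the camera method, from the composition values, or from the two offsetting each other.

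**Working it through.** **Step 1: trace the conversions (Study 3 and the nutritional content section).**

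| Method | Nutrients derived in | Composition table stated |
|---|---|---|
| Passive (images) | AIM | West or East African preferred; others in support |
| Weighed record | Dietplan | none named |
| 24-h recall | Dietplan | none named |

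**Step 2: split the error.** For one person-day, let g be the true grams of a food and t_D the nutrient content per gram assigned in Dietplan. Let g_P and g_R be the grams from images and recall, and t_A the content assigned in AIM. Summing over foods:

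- Passive − weighed = Σ(g_P − g)·t_A + Σ g·(t_A − t_D)
- Recall − weighed = Σ(g_R − g)·t_D, when recall and weighed entries receive the same food codes

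The second sum in the first line is the table and coding difference. It has no counterpart in the second line except where recall and weighed entries are coded differently. In grams alone it vanishes for both methods.

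**Step 3: illustrate with perfect foods and grams.** The article gives no table difference, intake CV or portion error, so there is no plan figure to reproduce and every input below is an assumption. Set the weighed record to mean 1 and CV c, and let AIM values be (1+b) times Dietplan values for every food. Then

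CCC = 2(1+b)c² / [c² + (1+b)²c² + b²].

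For b = +0.10 and c = 0.3: 2(1.10)(0.09) / [0.09 + 1.21(0.09) + 0.01] = 0.198 / 0.2089 = 0.948.

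| b | CCC, c = 0.2 | CCC, c = 0.3 | CCC, c = 0.4 | ±10% rule |
|---|---|---|---|---|
| +5% | 0.970 | 0.986 | 0.991 | met |
| +10% | 0.894 | 0.948 | 0.968 | met, nothing left |
| −10% | 0.874 | 0.937 | 0.961 | met, nothing left |
| +15% | 0.797 | 0.894 | 0.934 | failed |
| −15% | 0.744 | 0.862 | 0.912 | failed |

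With b = 0 the CCC is 1.000 throughout.

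**Step 4: give passive and recall the same portion error.** Assume −5% bias and multiplicative noise with CV e = 0.15 for both, with c = 0.3. The passive net bias is n = 0.95(1+b) − 1; for the recall n = −0.05. Then

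CCC = 2(1+n)c² / {c² + (1+n)²[c² + e²(1+c²)] + n²}.

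- Recall: 0.171 / (0.09 + 0.1034 + 0.0025) = 0.873.
- Passive, b = −10%: n = 0.95 × 0.90 − 1 = −0.145; CCC = 0.1539 / (0.09 + 0.0837 + 0.0210) = 0.790.

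| b | Passive net bias | Passive CCC | Recall CCC |
|---|---|---|---|
| −10% | −14.5% (fails ±10%) | 0.790 | 0.873 |
| 0 | −5% | 0.873 | 0.873 |
| +5% | −0.25% | 0.880 | 0.873 |
| +10% | +4.5% | 0.866 | 0.873 |

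Two methods with equal portion error separate in either direction, depending only on b. At b = +5% the portion bias is almost entirely hidden.

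**The case against.** **The tables may be the same.** A reader might infer that the food tables differ. The article does not say so: it never names Dietplan's tables, and AIM can load several databases. Only the split in software and staff is stated. The AIM section's matching rule might also be read as covering all foods in the study, but that section is about images and does not mention Dietplan. This objection stands against any claim that the tables differ; it does not show that a common table is fixed.

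**This is a condensed article.** Code lists and recipe handling are often left to a full protocol or coding manual, and silence on them alone would be no finding. The point rests instead on what the article states: different systems for the passive method and its reference, and one shared system for the recall and that reference.

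**The passive method is an end-to-end system.** The devices section includes nutritional analysis in it, so testing it as deployed, against independently coded records, is a legitimate aim. That holds as a rationale for reporting the as-deployed result. It does not make the contrast with the recall fair, and because AIM allows a choice of database, the table is a setting and not a fixed property of the camera.

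**A uniform multiplier is a severe illustration.** This is fair. Differences that vary in sign between foods would partly cancel in daily totals, and may be small for energy and larger for some micronutrients.

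**Conclusion.** The asymmetry is stated in the article and bears on the ±10% nutrient rule and on the bootstrap comparison of CCCs. Both are confounded, to an unknown extent, by any table or coding difference between AIM and Dietplan.

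Three stronger readings are not supported:

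- A reader might infer that the comparison is tilted against the passive method. Step 4 shows that a difference can also flatter it.
- A reader might infer that the trial has no means of telling camera error from table error. Portion-size agreement is among the planned outcomes and does not depend on composition values, so good agreement in grams with poor agreement in nutrients would point to coding or tables. It does not repair the accuracy rule, which is set on nutrient intake.
- A reader might infer that the recall is wholly untouched. Cancellation is complete only if recall and weighed entries receive the same food codes, which the article does not state.

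The figures of a fully used ±10% allowance and a CCC of about 0.95 assume a uniform 10% difference, perfect grams and an intake CV of 30%. None of these comes from the documents.

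**What to change.** For the Study 3 energy and nutrient comparisons, export grams per food from each of the three methods and apply one composition file per country to all of them, with the same database hierarchy, food codes and recipes. Working from exported grams avoids relying on Dietplan to accept a shared file. Keep the coders of each method blind to the others; this is compatible with a shared table and preserves the independence already planned.

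If that is not feasible, at minimum re-code the weighed records and recalls with the AIM tables as a sensitivity analysis, and repeat the ±10% assessment and the bootstrap comparison on those values. In either case report portion-size agreement in grams separately. If a common table is already in use, a sentence in the protocol or SAP naming it for all three methods would settle the question of tables; shared food codes and recipes should be stated with it.

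The cost is a modest amount of work to build and apply the shared file, plus the wording change. No further participants or field data are needed. The trade-off is that the as-deployed AIM nutrient output becomes a secondary analysis.

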### Assessment of dietary intake

This study aims to develop an objective, passive method for accurate estimation of an individual's food and nutrient intake. To facilitate this, the study will explore different image analysis methods to help develop reliable, accurate, and cost-effective backend software capable of automatic food recognition, estimation of portion size, and nutritional content of foods on images captured by the devices in the households (**Figure 2**). The different methods proposed for achieving these nutritional outcomes are described below.

**FIGURE 2 fig2:**
[figure not shown]
A schematic diagram of the study plan. Wearable and fixed camera devices will be used to collect images of food intake and related activities such as cooking in households in Ghana and Uganda. Images captured by the devices will be stored in cloud storage, and the stored food images will be used for food recognition and estimation of portion size and nutrient content, thus providing objective, passive dietary assessment.

#### Food image recognition

The convolutional neural network (CNN) method, a start-of-the-art deep learning technique used in image recognition (25), will be used to enable automatic recognition of images of foods captured in this study. CNN reveals intricate structures/features on input data (e.g., pixel value of an image) through transforming the raw data into a suitable internal representation, which the learning subsystem can detect and classify. Images of foods consumed in Ghana and Uganda will be collected for the creation of a food image dataset, and to train the neural network to recognize the food on the images. CNN will be validated against nutritionist-annotated images to determine its accuracy, before its application on the actual study food images.

#### Portion size estimation

This study will use the images of foods captured by the devices to quantify the amount of each food an individual consumed in a day. This will be achieved using the following methods.

##### Visual estimation

This method relies on a trained eye to estimate visually the quantity of food on images. To do this accurately, the assessor should be familiar with the local foods as well as having knowledge of the use of aids for portion size estimation. In this study, dedicated local staff in Ghana and Uganda will be trained to perform the visual portion size estimation. Training will consist of: *1*) learning the method of estimation; *2*) practicing the estimation on a standard practice deck of images with known portion sizes of food; and *3*) testing on a selection of images not included in the practice deck. Each assessor will be retested every 3–6 mo to track consistency and accuracy, and additional practice will be conducted if needed before retesting.

Food images for each eating occasion will be viewed using custom software, the AIM software (**Figure 3**). The portion size for each food will be estimated from images captured at the beginning and end of each eating occasion. However, all images for each entire eating occasion will be viewed to determine if additional portions of food were added to or subtracted from the plate or bowl before the end of the eating occasion, and if so the portion size of the additions and subtractions will also be estimated and taken into account to compute total consumption. An example of an addition would be a person taking a second helping; an example of a subtraction would be a person sharing the food on their plate with another person (e.g., a mother feeding a toddler from a common plate). A combination of portion size aids and comparison of food with common reference objects will be used to estimate portion sizes. The reference objects will include serveware (plates, bowls, cups, eating utensils, etc.) and hands/fingers appearing in images next to the foods and beverages. Foods not directly estimated in grams or kilograms will be estimated in volume (e.g., milliliters) and converted to grams using an estimated density (grams per milliliter) from INFOODS (International Network of Food Data Systems) (26, 27) and other sources such as USDA Food Composition Databases.

**FIGURE 3 fig3:**
[figure not shown]
The Automatic Ingestion Monitor (AIM) software—an image annotation and dietary intake assessment software. AIM distinguishes between eating (blue bars, bottom left) and noneating episodes. Clicking on the blue bar displays images from the detected eating event. The images can be browsed individually and magnified to provide a good view of all the foods on the image. The software supports the incorporation of standard food composition databases. The software also supports visual estimation of portion sizes.

##### Mathematical model

This method estimates food volume using a mathematical model/equation. This model relies on the measurements (height and diameter/width) of serveware (i.e., cups, bowls, plates, basins etc.) and cookware (i.e., pot and pans) used in the household, as a reference scale. To obtain the reference scale, field staff in the 2 countries will arrange to visit the households to measure and record the height and width of the serveware household members use to eat. Image captured by a wearable device at the beginning and end of an eating episode will be used to estimate the volume of food consumed using the formula: 
(1)}{}$$\begin{eqnarray*}
V = \frac{{\pi kl{d^2}h}}{4}
\end{eqnarray*}
$$where *V* represents the estimated volume, *k* is the shape parameter, *l* is the level parameter, *d* is the diameter/width of the serveware, and *h* is the height of the serveware. The shape parameter (*k*) can be obtained using 2 methods. In the first method (the precise method), the serveware (e.g., a bowl) is filled with water to its brim to measure and record (in grams) the net weight of water the serveware contains. The parameter *k* is then obtained by dividing the net weight of water [which has the same value in grams as the volume in milliliters (i.e., 1 g ≡ 1 mL)] in the serveware by the calculated volume (also in milliliters) of a hypothetical cylinder having the same diameter and height as the serveware. In the second, which is the approximate method, *k* is selected empirically from a range between 0.5 and 0.8, depending the shape of the serveware. The level parameter (*l*), which represents the fill level of bowl or cup, is visually estimated from the captured image. In this method, *l* must be chosen under the condition 0 < *l* ≤ 1, where 0 and 1, respectively, correspond to “completely empty” and “completely full.”

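### The mathematical model takes food consumed from start and end images with no step for food added or given away mid-meal, although visual estimation of the same quantity requires that step

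*Protocol article*

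**What the plan says.** The Portion size estimation section offers three ways to quantify how much of each food a person ate in a day: visual, mathematical and computational.

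- **Visual estimation** begins with two time points: "The portion size for each food will be estimated from images captured at the beginning and end of each eating occasion". It does not stop there. It continues that "all images for each entire eating occasion will be viewed to determine if additional portions of food were added to or subtracted from the plate", and that "the portion size of the additions and subtractions will also be estimated and taken into account to compute total consumption". On what counts as an addition it says: "An example of an addition would be a person taking a second helping". Its example of a subtraction is a person sharing food from the plate.
- **Mathematical model** uses the same two time points: "Image captured by a wearable device at the beginning and end of an eating episode will be used to estimate the volume of food consumed". The formula is V = πkld²h/4. Here d and h are measured on the serveware and k is a shape parameter. The level parameter l is described as one "which represents the fill level of bowl or cup, is visually estimated from the captured image". The section mentions no other images and has no step for food that enters or leaves the container during the episode.
- **Computational estimation** describes how a volume is obtained from an image. It does not say how volumes are combined into an amount eaten.

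The Analytical plan calls a method accurate when its nutrient estimates fall within ±10% of the weighed food record.

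**The concern.** The protocol recognises, under one estimator, that start and end images do not by themselves give total consumption. It supplies the correction there. For a second estimator of the same quantity it names the same two time points and gives no correction. Neither the introduction to Portion size estimation nor the model section carries the step across.

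If the model is applied as written, the two estimators measure different things on any meal with a refill or with food handed on. The errors run in opposite directions: people who take seconds are under-counted, and people who give food away are over-counted. A comparison of the two estimators would then mix error in reading volumes with a difference in what is being measured. More careful measurement of the bowls would not remove it.

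**Working it through.** **Inputs from the protocol article**

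- V = πkld²h/4, with l read from one image, so V is the content of the container at one moment (Mathematical model).
- k by the approximate method "is selected empirically from a range between 0.5 and 0.8, depending the shape of the serveware".
- Accuracy limit: ±10% of the weighed record (Analytical plan).

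The article states no figure for this error, so there is none to reproduce first. It also does not write out the subtraction of the end volume from the start volume. I take that as the natural reading of how two images yield an amount consumed.

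**Mass balance for one episode.** Let A be food added and S food given away between the two images.

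- Model estimate: M = V(start) − V(end)
- True intake: T = V(start) + A − S − V(end)
- Error: M − T = S − A

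The error is zero only when A and S are both zero or happen to be equal.

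**Illustration (assumed values).** Take a bowl with d = 16 cm and h = 7 cm, with fill level falling from 0.8 to 0.1. Capacity is πk(16²)(7)/4, which is 704, 915 and 1,126 mL for k = 0.5, 0.65 and 0.8. M is 0.7 of capacity: 493, 640 and 788 mL. Write A and S as shares of capacity. The relative error is then 0.7/(0.7 + A − S) − 1, in which k, d and h cancel.

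| Mid-meal change (share of capacity) | Calculation | Error |
|---|---|---|
| Second helping 0.1 | 0.7/0.8 − 1 | −12.5% |
| Second helping 0.2 | 0.7/0.9 − 1 | −22.2% |
| Second helping 0.4 | 0.7/1.1 − 1 | −36.4% |
| Given away 0.1 | 0.7/0.6 − 1 | +16.7% |
| Given away 0.2 | 0.7/0.5 − 1 | +40.0% |
| Given away 0.4 | 0.7/0.3 − 1 | +133.3% |
| 0.2 added and 0.2 given away | 0.7/0.7 − 1 | 0% |

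**When the ±10% limit is passed**

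- Additions only: M/(M + A) < 0.9 when A > M/9, that is 11.1% of M.
- Subtractions only: M/(M − S) > 1.1 when S > M/11, that is 9.1% of M.
- Both say the same thing: the net uncorrected amount exceeds 10% of true intake. The same holds for a whole day, with the net amount and true intake summed over the day.

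The limit is stated for nutrients and this calculation is in volume. The two agree when the food added or given away has the same composition as the rest of the food eaten. A different food would change the nutrient error.

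**With the correction.** Using V(start) − V(end) + A − S makes the error from this source zero.

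**The case against.** The strongest reply is that the model section does not say that only the two images are used. Visual estimation opens with almost the same statement and then adds the review, so the model section may be giving the base step of a geometry sketch. A condensed article may leave the handling of refills to a full protocol or coding manual. This lowers certainty, but it does not remove the conflict: the article itself states two rules for one quantity and attaches the correction to one of them.

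The weighed food record is also described by weights before and after eating, with no mention of refills. Read as literally, the reference would share the omission. The errors would then partly cancel in the comparison while both intakes stayed wrong. If the weighed record does capture every serving, the full S − A enters the comparison. The article does not settle which.

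Three stronger readings are tempting and are not supported:

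- A reader might infer that Study 1 invites the error, because "Participants will be asked to eat until full". That section describes pre-weighed food and weighed leftovers, with no refills. The serveware measurements that the model needs are taken in households in Ghana and Uganda.
- A reader might infer that adults who feed children from their own plate are common, since households qualify by having young children or adolescents. The article gives no frequency. For shared-plate eating it makes partial separate provision through Foodcam and, in selected households, a 360° camera. That provision does not cover second helpings or food handed from an individual plate.
- A reader might infer that the computational method has the same flaw. Its section states no start-and-end rule, so there is none to correct. It only needs the same definition of consumption where its volumes are turned into intake.

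**Conclusion.** The point holds as an inconsistency between two stated rules for the same quantity. On the plain reading, the model's error in an episode is exactly S − A, and an episode breaches ±10% from this source alone once the net uncorrected amount exceeds 10% of true intake. That result depends only on reading consumption as start volume minus end volume. The percentages in the table also rest on an assumed fill level and assumed amounts added or given away.

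A reader might go on to infer a definite bias in the study's mean intake, or a failed validation. The document does not support either. It gives no frequency or size of refills or sharing, the two directions offset each other in a mean, and the Analytical plan does not say which portion-size estimator supplies the passive method's values. The effect on the concordance coefficient, the Bland–Altman limits and the paired tests is therefore unknown. The correction is still worth making, because it is specific and nearly free.

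**What to change.** Add to the Mathematical model section that all images of the episode are reviewed as under Visual estimation, and that

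consumed = V(start) − V(end) + Σ additions − Σ subtractions,

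with V computed from the image just before and the image just after each change, so that each addition or subtraction is the difference between the two. Where computational volumes are used to derive intake, apply the same definition, so that all three estimators target one quantity.

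The cost is small. The wearable cameras already record throughout eating, and the whole-occasion review is already required for visual estimation. What is added is one or two sentences in the protocol and a few extra fill-level readings on meals with a refill or food given away.
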